## Abstract

**Background:**

The death of a partner is a critical life event in later life, which requires grief work as well as the development of a new perspective for the future. Cognitive behavioral web-based self-help interventions for coping with prolonged grief have established their efficacy in decreasing symptoms of grief, depression, and loneliness. However, no study has tested the efficacy for reducing grief after losses occurring less than 6 months ago and the role of self-tailoring of the content.

**Objective:**

This study aims to evaluate the clinical efficacy and acceptance of a web-based self-help intervention to support the grief process of older adults who have lost their partner. It will compare the outcomes, adherence, and working alliance in a standardized format with those in a self-tailored delivery format and investigate the effects of age, time since loss, and severity of grief at baseline as predictors. Focus groups to understand user experience and a cost-effectiveness analysis will complement the study.

**Methods:**

The study includes 3 different randomized control trials. The trial in Switzerland comprises a waitlist control group and 2 active arms consisting of 2 delivery formats, standardized and self-tailored. In the Netherlands and in Portugal, the trials follow a 2-arm design that will be, respectively, complemented with focus groups on technology acceptance and cost-effectiveness analysis. The main target group will consist of adults aged >60 years from the general population in Switzerland (n≥85), the Netherlands (n≥40), and Portugal (n≥80) who lost their partner and seek help for coping with grief symptoms, psychological distress, and adaptation problems in daily life. The trials will test the intervention’s clinical efficacy for reducing grief (primary outcome) and depression symptoms and loneliness (secondary outcomes) after the intervention. Measurements will take place at baseline (week 0), after the intervention (week 10), and at follow-up (week 20).

**Results:**

The trials started in March 2022 and are expected to end in December 2022 or when the needed sample size is achieved. The first results are expected by January 2023.

**Conclusions:**

The trials will provide insights into the efficacy and acceptance of a web-based self-help intervention among older adults who have recently lost a partner. Results will extend the knowledge on the role of self-tailoring, working alliance, and satisfaction in the effects of the intervention. Finally, the study will suggest adaptations to improve the acceptance of web-based self-help interventions for older mourners and explore the cost-effectiveness of this intervention. Limitations include a self-selective sample and the lack of cross-cultural comparisons.

**Trial Registration:**

Switzerland: ClinicalTrials.gov NCT05280041; https://clinicaltrials.gov/ct2/show/NCT05280041; Portugal: ClinicalTrials.gov NCT05156346; https://clinicaltrials.gov/ct2/show/NCT05156346

**International Registered Report Identifier (IRRID):**

PRR1-10.2196/37827

## Introduction

### Background

The death of a partner is a very stressful critical life event in later life. It involves a dissolution of social and emotional ties, which requires the acceptance of the loss as well as the development of a new identity and a new perspective for the future. It involves the adaptation of daily routines, which can be even more challenging when social, physical, and financial resources decrease in later life [1]. Grief and psychological distress after the loss of a partner are normative reactions. For most individuals, grief intensity weakens to a manageable degree within several weeks or months after the loss (eg, [2,3]). However, some individuals are less able to cope with bereavement and show symptoms of prolonged grief or adaptation problems [4-7]. Approximately 10% of mourners develop prolonged grief, which is a psychological disorder characterized by separation distress; frequent or disabling cognitive, emotional, and behavioral symptoms such as avoidance of reminders of the loved one; difficulties moving on with life; and functional impairment [8-10]. A recent study comparing the prevalence of prolonged grief disorder based on 2 criteria sets, Diagnostic and Statistical Manual of Mental Disorders, Fifth Edition, American Psychiatric Association [11] and International Statistical Classification of Diseases and Related Health Problems, 11th Edition, World Health Organization, 2019 [12], found a lower prevalence of the disorder (4.4% and 3.3%, respectively) than the previous studies. However, this study highlighted a higher prevalence of symptoms: difficulty accepting the loss was the most frequent single symptom (14%-25%), and grief-related impairment was common (10%-16%). Crucially, this study showed that >60% of participants with probably prolonged grief disorder used health care services [13]. Therefore, supporting mourners and promoting a healthy grief process is key to preventing further health problems.

### Web-Based Grief Interventions

Several web-based interventions have been developed as a complement to face-to-face grief counseling or therapy [14-18]. A recent meta-analysis, while summarizing the evidence for web-based interventions for mourners, found that all the cognitive behavioral therapy (CBT)–based interventions showed moderate effects (*g*=0.54) for symptoms of grief and large effects (*g*=0.86) for posttraumatic stress disorder, with effects being stable over time [19]. Furthermore, an additional systematic review and meta-analysis with similar aims managed to replicate said results, showing that all 9 assessed randomized controlled trials decreased symptoms of grief after bereavement [20]. However, this meta-analysis clarified that most of the interventions assessed focused on the loss of a child. Only 2 interventions focused on the loss of the partner and on prolonged grief [14,15]. From these, only 1 study aimed at supporting the grief process of older adults [14]. This suggests that the bereavement of older adults when they lose their partners is overlooked, especially considering the potential for developing prolonged grief and other symptoms. Indeed, older adults seem to be underrepresented in web-based CBT interventions in general, as suggested by a meta-analysis testing whether computerized CBT treatments are potential tools to decrease depression in later life [21]. Despite being pervious to challenges related to low digital literacy, web-based interventions aimed at older adults present several benefits such as high accessibility, flexibility, and privacy as well as low costs [22]. Such benefits are expected to outweigh these potential barriers.

CBT techniques such as exposure, cognitive reappraisal, as well as integration and restoration as treatment components have been demonstrated to have good results in web-based self-help interventions for complicated grief after bereavement [17,18]. Furthermore, a study compared exposure on the web with behavioral activation treatment [15], showing that both interventions reduced complicated grief, posttraumatic stress, and grief rumination, but only exposure showed an effect on depression and brooding levels relative to the control group. Most web-based interventions provide standardized modules in a given order. However, the need to achieve better outcomes by adapting treatment planning to each individual has been guiding research in face-to-face CBT interventions (eg, [23]). It also fostered the development of modular intervention formats, which proved to be effective (eg, [24,25]). Rather than following a standardized fixed order, in this type of intervention, modules are implemented according to individuals’ specific symptoms and specific needs at each time (eg, [25]). Following this principle, self-tailored, web-based CBT interventions (iCBT) may lead to promising results as modular face-to-face approaches. A study addressing comorbidity in depression compared self-guided iCBT with standardized (nontailored) iCBT and revealed that both delivery formats of the intervention improved measures of depression, anxiety, and quality of life. This study also revealed that the self-tailored treatment was more effective than the standardized treatment among participants with more severe symptoms at baseline and more comorbidity [26]. However, most of the research tends to compare web-based interventions (regardless of being self-tailored or standardized) with other therapeutic formats, such as care-as-usual or discussion groups, as it is described in a meta-analysis testing the role of self-tailoring in web-based interventions [27].

### The Web-Based Self-help Intervention

The development and evaluation of the web-based self-help intervention for mourners is embedded in the Optimizing the Mental Health and Resilience of Older Adults That Have Lost Their Spouse via Blended, Online Therapy (LEAVES) project [28], a European project, funded by the Active and Assisted Living Programme focused on the development of a web-based self-help program that supports older adults dealing with the loss of their partner and with adapting to the new life situation. The web-based self-help intervention is based on 2 theoretical models describing crucial factors for an adaptive adjustment to bereavement: the 4 tasks of mourning [29] and the dual-process model of coping with bereavement [30,31]. It follows the most relevant CBT elements that cognitive behavioral interventions for prolonged grief are often based on (1) exposure (eg, telling the story of the loss), (2) cognitive reappraisal or restructuring of individual dysfunctional thoughts (eg, guilt or anger) associated with the loss, (3) integration and restoration including self-care and social re-engagement, and (4) behavioral activation [32,33]. As described earlier, previous web-based grief interventions have been testing the benefits of these elements (eg, [15]), although these studies did not combine the 4 elements in a single intervention, as it is the aim of this web-based self-help program. The content of the intervention is based on the LIVIA self-help program for coping with prolonged grief after the loss of a spouse [14,34,35]. LIVIA, as a text-based intervention on the web, without sophisticated interaction with users, proved its efficacy for mourning older adults from a general Swiss population sample with a mean age of 59 years, who had lost their partner at least 6 months ago. It confirmed that the intervention is also efficacious for milder grief symptoms and thus may prevent grief-related disorders. Compared with the waitlist control group, the intervention resulted in significant reductions in grief (Cohen *d*=0.81), depression (Cohen *d*=0.59), and psychopathological distress (Cohen *d*=0.39) as primary outcomes and reductions in embitterment (Cohen *d*=0.37) and loneliness (Cohen *d*=0.37) and an increase in life satisfaction (Cohen *d*=−0.41) as secondary outcomes. These gains were maintained over 3 months. Improvements were similar among participants with low, medium, or high levels of grief at baseline.

The content of the LIVIA program, based on the elements of exposure, cognitive reappraisal, and restoration, has been complemented with an Activities section for behavioral activation, as well as a conversational virtual agent that guides users through the self-help program. In distinct modules, the program provides users the opportunity to cope with their grief in a thorough process from confrontation with the loss to practicing new coping strategies and routines focused on the adaptation to a new life.

### Research Goals

This study has five research goals: (1) to test the efficacy of the web-based self-help program in 3 countries, which includes comparing the active arms with a control group; (2) to examine which delivery format (standardized vs self-tailored) leads to better clinical outcomes; (3) to investigate the mechanisms of change underlying the intervention effects and to examine the roles of predictor variables and mediators; (4) to assess technology acceptance from the perspective of older adults in grief; and (5) to estimate the cost-effectiveness of the web-based service for providers to support the business models and marketing strategies during the implementation of the service. Thus, it provides a comprehensive evaluation of the web-based self-help program.

### Main Research Hypotheses

The main research hypotheses include the following:

We hypothesize that the intervention will significantly decrease grief symptoms (primary outcome) as well as depression symptoms and perceived loneliness (secondary outcomes) compared with the control group.Considering that the self-tailored delivery format provides participants with the opportunity to meet their specific needs at any time, we hypothesize that the self-tailored intervention will lead to higher satisfaction with the intervention and to a higher decrease in grief, depression symptoms, and perceived loneliness than the standardized intervention.We hypothesize that the overall helpfulness of the modules, gains in mastery experiences, self-esteem, insights, the matching of the needs of the user (session outcomes), and a better working alliance mediate the effect of the treatment.Comparing the 2 active arms, we hypothesize that the self-tailored intervention will lead to better session ratings and a higher working alliance than the standardized intervention, thus leading to better outcomes after the intervention.

To better understand the intervention effects, exploratory analyses will test whether age, time since loss, and the severity of grief symptoms affect treatment outcomes. Technology acceptance and cost-effectiveness analysis are exploratory and have no a priori hypotheses.

## Methods

### Study Paradigm

The intervention’s efficacy will be tested in Switzerland, Portugal, and the Netherlands, in 3 different trials. Besides the main goal of testing efficacy, each trial will allow meeting different complementary research goals and, consequently, will follow different designs. In the study conducted in Switzerland, the complementary goal will consist of a thorough efficacy evaluation, including the comparison of a standardized with a self-tailored intervention. It consists of a 3-arm randomized controlled trial with 2 active arms (standardized vs self-tailored) and a waitlist control arm and will explore clinical mediators and predictors of the intervention’s effect. Following the principle of parsimony, the trials in the Netherlands and Portugal will follow variations of the main clinical design using a 2-arm randomized controlled trial comparing the intervention with a control group; whereas in the Netherlands trial, whose complementary research goal is to understand technology acceptance, the self-tailored intervention will be compared with a waitlist group. The focus on technology acceptance will be implemented through the conduct of focus groups. In Portugal, where the complementary goal will be to conduct a cost-effective analysis, the study will compare the standardized intervention with a care-as-usual group. The study in Portugal will also include qualitative methodology for the assessment of the barriers to and facilitators of using the web-based self-help program. Testing the web-based self-help intervention in 3 countries is not intended to guide cross-cultural comparisons but to inform different complementary research goals. The web-based intervention will be named differently in the 3 countries: SOLENA in Switzerland, EuLuto in Portugal, and LEAVES in the Netherlands.

### Participants

The main target group is older mourners from the general population (adults aged >60 years) who have lost their partner and seek help in their grief process. Specific inclusion criteria are (1) experience of partner bereavement; (2) seeking help or willingness to accept help to cope with grief symptoms, psychological distress, or the psychosocial adaptation to a life without the deceased; (3) access to an internet connection and adequate equipment; (4) mastery of the country’s first language; and (5) an informed consent by the participant. General exclusion criteria are (1) that the loss occurred <1 month before enrolling in the study, (2) severe psychological or somatic disorders that need immediate treatment and hinder the continuous work on the web-based self-help program, (3) acute suicidality, (4) no emergency plan that specifies a health care professional or service who participants can turn to if they find themselves in crisis, and (5) cognitive or physical inability to follow the procedures of the study. Considering that this research does not have an age-related hypothesis, the trials do not impose an age limit for the participants.

### Sample Size

Sample size was determined by a power analysis based on a probability level of 0.05 and a power of 0.80 with G*Power [36], which is based on the results of the evaluation of LIVIA [14]. As in LIVIA, we expected a large effect size of Cohen *d*>0.80 for the decrease in grief as primary outcome, measured by the Texas Revised Inventory of Grief (TRIG), in the comparison of the intervention with a waitlist control group or care-as-usual control group. For the comparison of the standardized intervention with the self-tailored interventions, we expect a small to moderate effect (Cohen *d*=0.30) in favor of the self-tailored version. Power analyses for a repeated measures ANOVA with a within-between interaction for 3 groups in Switzerland estimated a sample size of at least 85 participants. For the 2-arm designs in Portugal and the Netherlands, we anticipate a dropout rate of 15% and, consequently, efforts will be made to recruit more primary end users than indicated by the power analysis.

For the target group of primary end users, older mourners, the aim is to include at least 85 participants in the study conducted in Switzerland with an allocation of 35:35:15 for the 2 active arms and the waitlist control group, respectively; at least 80 participants in Portugal with an allocation of 40:40; and at least 40 participants in the Netherlands, with an allocation of 20:20.

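### The Swiss sample of 85 is sized on a 3-group interaction and leaves the main hypothesis that self-tailored beats standardized with about 24% power at the stated d=0.30

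*Protocol article*

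**What the plan says.** The protocol article's Sample Size section describes a G*Power calculation "based on a probability level of 0.05 and a power of 0.80". It names two expected effects: at least 0.80 for intervention against control ("we expected a large effect size of Cohen *d*>0.80 for the decrease in grief as primary outcome"), and d=0.30 for self-tailored against standardized. For Switzerland it then says that a repeated measures ANOVA with "a within-between interaction for 3 groups in Switzerland estimated a sample size of at least 85 participants", and sets the target "with an allocation of 35:35:15 for the 2 active arms and the waitlist control group". It gives no power for any two-arm comparison. The 15% dropout is stated only for the two-arm trials in Portugal and the Netherlands.

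Main Research Hypotheses includes the format comparison: the self-tailored version is to produce "a higher decrease in grief, depression symptoms, and perceived loneliness than the standardized intervention". Research Goals lists it as the second of five goals, Study Paradigm names it within the Swiss trial's complementary goal, and Expected Findings says the Swiss trial will test it.

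Limitations and Future Directions concedes that a larger sample may be needed, but only for the mediation analysis.

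**The concern.** One significance level, one power and two effect sizes stand in a single paragraph, followed by one total sample size. A reader will naturally take both effects as covered at 80%. But the test named is an interaction across three groups. It can be significant because both active arms beat the waitlist, even if the two formats do not differ. Power for that test therefore says little about power for the format contrast, which has one degree of freedom and rests on the two arms of 35.

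The format comparison is a main hypothesis and is what sets the Swiss design apart from the other two trials. If a true difference of 0.30 SD would usually be missed, the plan should say so before the data are seen. It should also say what a non-significant result can and cannot support.

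**Working it through.** **The plan's own figure.** The 85 cannot be recomputed, because the article gives no Cohen f, number of measurements or pre-post correlation. For three groups and N=85, 80% power on the within-between interaction (noncentrality f²·N·m/(1−ρ)) is reached at several settings: f of about 0.171 with m=2 and ρ=0.5, 0.153 with m=2 and ρ=0.6, or 0.155 with m=3 and ρ=0.5. So 85 is neither confirmed nor refuted. A condensed article may leave these inputs to the full protocol.

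**Inputs for the format contrast.** From Sample Size: alpha 0.05 (sidedness not given, taken as two-sided), d=0.30 and 35 per arm. Assumption: ρ is not stated, so 0.3 to 0.8 is shown, with d in units of the outcome SD.

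**Formulas.** Statistical Analyses plans a pre-post time-by-group model. With complete data this is the comparison of change scores, whose SD is s = √(2(1−ρ)). With baseline adjustment, s = √(1−ρ²). The noncentrality is δ = (d/s)/√(1/n₁+1/n₂), and power comes from the noncentral t with n₁+n₂−2 degrees of freedom.

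**Change score, ρ=0.5.** s = 1, √(2/35) = 0.239, δ = 0.30/0.239 = 1.255 on 68 df. Power is 23.6%.

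| ρ | Change score | Baseline-adjusted |
|---|---|---|
| 0.3 | 18% | 25% |
| 0.5 | 24% | 30% |
| 0.6 | 28% | 34% |
| 0.7 | 36% | 41% |
| 0.8 | 50% | 54% |

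Further results for this contrast, at ρ=0.5 on the change score unless noted:
- A one-sided test has 34%.
- With an assumed 15% loss (0.85 × 35 ≈ 30 per arm), power is 21%.
- 80% needs ρ of about 0.90 under either analysis, or d of about 0.68 with 35 per arm, or 176 per arm at d=0.30.
- The 95% CI half-width is 1.96 × 0.239 ≈ 0.47 SD, wider than the 0.30 sought. At ρ=0.8 it is 0.47 × 0.632 ≈ 0.30 SD.

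**Why the 3-group test can look adequate.** Take the section's own effects as changes of 0.80 (standardized), 1.10 (self-tailored, 0.30 better) and 0 (waitlist). The weighted mean is (35×0.80 + 35×1.10)/85 = 0.782. At ρ=0.5 the noncentrality is 35(0.018)² + 35(0.318)² + 15(0.782)² ≈ 12.7, giving 89% on 2 and 82 df. The waitlist term alone, 15 × 0.782² ≈ 9.2, is most of that. The same 85 people therefore give 89% for the omnibus test and 24% for the format contrast.

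**Secondary: against the waitlist, d=0.80, ρ=0.5, before any loss.**

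| Contrast | Change score | Baseline-adjusted |
|---|---|---|
| One arm, 35 v 15 | 72% | about 84% |
| Pooled, 70 v 15 | 79% | 89% |

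With an assumed 15% loss, the change-score figures fall to 65% and 73%.

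**The case against.** The strongest reply is that the article never claims 80% power for the format comparison. Read literally, the 0.80 belongs to the 3-group interaction, and on the section's own effects that test has 89% at ρ=0.5. This stands. A reader might infer that the sample fails to deliver its stated power, but the article does not support that for the test it names. The 89% is itself conditional: it is 76% at ρ=0.3, and 70% at ρ=0.5 if both active arms equal 0.80. What survives the reply is that the omnibus test does not answer the format hypothesis.

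Three further inferences are tempting and should not be drawn:
- **A flat 72% for either active arm against the waitlist.** The article gives 0.80 as a floor and cites 0.81 from the earlier LIVIA evaluation. It also expects self-tailored to do better: at d=1.10, 35 against 15 has 94%. Its efficacy hypothesis concerns the intervention as a whole, and baseline adjustment or ρ of about 0.6 takes a single arm past 80%.
- **That 85 came from entering one particular Cohen f.** Several combinations of f, ρ and number of measurements give 85, so this would be conjecture.
- **That the Dutch trial of 20:20 is too small for efficacy.** At d=0.80 and ρ=0.5 it has 69% on the change score but 81% with baseline adjustment. The plan also says it will try to recruit beyond the calculated number because of dropout.

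The targets are minimums, and the 15% loss applied to Switzerland above is an assumption. Finally, nothing in the article plans an equivalence claim. The wording proposed on that point is a precaution, not the correction of a stated error.

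**Conclusion.** The point holds for the format comparison. A main hypothesis with its own stated effect of d=0.30 has about 24% two-sided power at 35 against 35 with ρ=0.5 on the change score. Over ρ from 0.5 to 0.8, and across both analyses, the range is 24% to 54%. At ρ=0.5 on the change score, a true difference of that size would be missed about three times in four. No correlation up to 0.8 and no choice between the two analyses brings power near 80%, and the article's acknowledgement about sample size does not extend to this hypothesis.

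The assumptions are a two-sided 5% test, equal SDs before and after, all 70 active-arm participants analysed unless loss is stated, and a correlation that the article does not give.

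Power against the 15-person waitlist is borderline rather than deficient. It is a secondary remark that turns on the correlation, the model, pooling and dropout, for which the Swiss target states no allowance.

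**What to change.** Amend the Sample Size section, with no added participants:

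1. State that the power of 0.80 refers to the 3-group within-between interaction and not to the comparison of the two formats.
2. State the power of the format comparison at d=0.30 with 35 per arm: about 24% to 54% for correlations of 0.5 to 0.8, naming the correlation assumed.
3. Make the format comparison an estimation objective, reported as a difference with its 95% CI (expected half-width about 0.47 SD at ρ=0.5). Say that a non-significant result will not be read as the formats being equivalent.
4. Where power against the waitlist is given, state it with its correlation, analysis model and dropout assumption, and say whether 85 includes any allowance for Swiss dropout.

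Main Research Hypotheses and Expected Findings should then describe the format comparison in the same terms. The cost is wording only. The price is a less favourable power statement for the format hypothesis.

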### Statistical Analyses

Dropout is defined as participants who withdraw actively from the study after randomization or fail to fill out the postintervention questionnaires despite 2 reminders. For technology acceptance, noncompliance is defined as not filling out the biweekly mood self-check questionnaire despite 2 reminders. Noncompliant participants are also defined as those who, despite not actively quitting the study, do not complete the 2 mandatory study modules (module 1 and module 2) within 10 weeks. Nevertheless, these participants will be a part of the intention-to-treat analysis, as they have been randomized. Adherence will be assessed with the number of modules completed and use data.

All rating scales will be checked for reliability (Cronbach α) and multicollinearity (correlation analysis). Results will be reported on scale averages, as well as multiple 2-way correlations. Analyses will be conducted according to the intention-to-treat paradigm. First, we will analyze the extent of missing data, explore the missing data patterns, and determine the type of missing data (missing completely at random, missing at random, or not missing at random). If the missing mechanism is missing at random, multilevel mixed effects regression analyses will be used, which allow a different number of measurement points per participant and are thus less sensitive to missing data.

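### The Swiss enrolment target equals the power-analysis number, with no stated allowance for dropout, so the stated 0.80 is not delivered at 85 enrolled once anyone lacks week-10 data

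*Protocol article*

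**What the plan says.** All the sample-size statements are in the protocol article, Methods, Sample Size.

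- The calculation is "a power analysis based on a probability level of 0.05 and a power of 0.80 with G*Power".
- For the Swiss trial, a repeated measures ANOVA with a within-between interaction "for 3 groups in Switzerland estimated a sample size of at least 85 participants".
- The enrolment target is set as follows: "the aim is to include at least 85 participants in the study conducted in Switzerland with an allocation of 35:35:15". The allocation sums to 35 + 35 + 15 = 85.
- Dropout enters in one sentence only: "For the 2-arm designs in Portugal and the Netherlands, we anticipate a dropout rate of 15" per cent. The same sentence draws the consequence that recruitment should exceed the power-analysis number. Nothing equivalent is said for Switzerland.

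Under Statistical Analyses, dropouts are those who actively withdraw after randomization or "fail to fill out the postintervention questionnaires despite 2 reminders". That definition is not restricted to any country. The analysis is by intention to treat, with mixed models using all available data.

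**The concern.** A power analysis returns the number of participants who must contribute the outcome. If enrolment is set at that same number, the stated power assumes that everyone enrolled supplies week-10 data. The authors know this, because in the same paragraph they respond to expected dropout in Portugal and the Netherlands by planning to recruit above the calculated number. For Switzerland the calculated number and the target coincide, and no Swiss dropout rate is given.

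At stake is the power claim for the only one of the three trials that compares the two delivery formats. That trial also carries an efficacy comparison against a waitlist arm of 15. If some Swiss participants do not return the week-10 questionnaire, a reader who relies on 0.80 is relying on a figure that the planned enrolment does not support.

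**Working it through.** **Inputs from the document.** Alpha and power: "a probability level of 0.05 and a power of 0.80". Three groups. Swiss N of at least 85 from the calculation, and at least 85 enrolled. Effects: "we expected a large effect size of Cohen *d*>0.80 for the decrease in grief as primary outcome" for intervention against control, and "we expect a small to moderate effect (Cohen *d*=0.30) in favor of the self-tailored version" for the format comparison. Dropout of 15%, stated for the two-arm trials only.

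**Inputs not in the document.** The effect size f entered in G*Power, the number of measurements m, and the correlation ρ between them.

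**Step 1. Can the 85 be reproduced?** For the within-between interaction with k groups, λ = f²·N·m/(1−ρ), df1 = (k−1)(m−1) and df2 = (N−k)(m−1). With f = d/2 = 0.30/2 = 0.15 and k = 3, the N for power 0.80 is:

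| m | ρ | N |
|---|---|---|
| 2 | 0.5 | 111 |
| 2 | 0.6 | 89 |
| 3 | 0.5 | 91 |
| 4 | 0.5 | 78 |

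With f = 0.80/2 = 0.40 and ρ = 0.5, N is 19 or fewer. So 85 lies inside the range that plausible settings produce, but it cannot be confirmed. The next step takes it at face value.

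**Step 2. Power when fewer than 85 have week-10 data.** Choose f so that power is exactly 0.80 at N = 85. With ρ = 0.5 this gives f = 0.171 for m = 2 (λ = 10.00) and f = 0.155 for m = 3 (λ = 12.29). Hold f fixed, so that λ shrinks in proportion to N. For example, at m = 2 and N = 72, λ = 10.00 × 72/85 = 8.47 on 2 and 69 degrees of freedom.

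| Assumed dropout | N with week-10 data | Power, m = 2 | Power, m = 3 |
|---|---|---|---|
| 0% | 85 | 0.80 | 0.80 |
| 5% | 85 × 0.95 ≈ 81 | 0.78 | 0.78 |
| 10% | 85 × 0.90 ≈ 77 | 0.75 | 0.75 |
| 15% | 85 × 0.85 ≈ 72 | 0.72 | 0.72 |
| 20% | 85 × 0.80 = 68 | 0.70 | 0.69 |

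The results are the same at ρ = 0.3, 0.5 and 0.7, because the calibration absorbs ρ.

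**Step 3. Pairwise check on the stated effects.** Two-sided t test with noncentrality d·√(n1·n2/(n1+n2)):

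- Both active arms against waitlist, d = 0.80. For 70 vs 15, 0.80 × √(1050/85) = 2.81 and power is 0.79. For 60 vs 13, 0.80 × √(780/73) = 2.61 and power is 0.73.
- Format comparison, d = 0.30. For 35 vs 35, 0.30 × √17.5 = 1.25 and power is 0.24. For 30 vs 30, 0.30 × √15 = 1.16 and power is 0.21.

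**Step 4. Enrolment needed to keep 85 with week-10 data.** At 15% dropout, 85/(1 − 0.15) = 100.

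**The case against.** **Both Swiss figures read as a minimum, so more may be enrolled.** True, but permission to exceed 85 is not a plan to do so. The Results section ties the end of the trials to December 2022 or to reaching the needed sample size, and for Switzerland the only stated size is 85. The Limitations section mentions a larger sample only for the mediation analysis.

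**The mixed model keeps dropouts in the analysis.** It does, but someone with only a baseline score carries almost no information about change by group at week 10. Intention-to-treat status does not replace the missing outcome.

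**15% is not a Swiss figure.** This stands. A reader might infer that the plan expects 15% in all three trials, but the text does not say so. Retention could differ: Swiss users get weekly coach feedback by email, Portuguese users a telephone contact every other week, and Dutch users passive support. Recruitment routes differ too. The paragraph is therefore incomplete about Swiss dropout; it does not contradict itself.

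**The loss is generic and conditional.** This also stands. The 0.72 follows from calibrating to 0.80 at 85; it is not derived from the sponsor's inputs. It also describes neither pairwise contrast: on the check above, dropout costs the format comparison only about 0.03 (0.24 to 0.21).

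**The small waitlist arm.** A reader might infer that the 15-person arm loses the most relative precision. It does not. Under uniform 15% dropout, the standard error of every arm mean rises by the same factor, 1/√0.85 = 1.085, and nothing in the document points to heavier loss on the waitlist.

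**Conclusion.** The point holds as a power statement that the stated enrolment does not deliver. At 85 enrolled, any Swiss dropout takes the number with week-10 data below the number on which 0.80 was computed. The shortfall is moderate: about 0.78 at 5% dropout and 0.69-0.70 at 20%. It rests on two assumptions: that the sponsor's calculation gives 0.80 at 85, and that Swiss dropout falls in the 5 to 20% range.

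It would be tempting to conclude that 0.80 is sound provided nobody drops out. The document does not support that either. Complete follow-up is necessary for 0.80 at 85 enrolled, but it has not been shown to be sufficient, because the 85 cannot be reproduced from what is stated.

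**What to change.** In Sample Size, state the dropout assumed for Switzerland and restate the Swiss power for the number expected to have week-10 data at 85 enrolled, recomputed from the sponsor's own G*Power inputs (f, number of measurements, correlation). If 15% is judged to apply, that is about 72 participants and, on the face-value calculation, a power of about 0.72; the printed figure should come from the sponsor's inputs. If 85 already includes an allowance, say so and give the uninflated number.

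Either statement costs a sentence and no extra participants, though the first makes the reported Swiss power less favourable. The alternative of relabelling 85 as the number required with week-10 data is not free: at 15% it implies enrolling about 100, which is 15 more.
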